Next to identification via the NCR and recruitment through hospitals, cancer survivors will be recruited through social media channels and (e-mail) messages of the Dutch Federation for Cancer Patient Organizations (NFK), Kanker.nl (a Dutch platform for cancer survivors), and psychosocial oncology walk-in centres (Instellingen PsychoSociale Oncologie; IPSO). Cancer survivors can contact the research team if they wish to receive aforementioned information package. This package will then be sent via post, after which the recruitment procedure is identical to that described above.

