### Sample size calculation

#### RCT among cancer survivors

The RCT sample size calculation is based on the primary self-reported outcome measure, i.e., working hours per week. Based on previous research [23], a standard deviation of 13 h per week was assumed, and a between group (intervention versus control) effect of 5.5 h per week is expected. Given this effect size, with a power of 80% and level of statistical significance set at *p*-value< 0.05, the sample size required is 88 cancer survivors in each group (176 in total). In this study 236 cancer survivors will be recruited, to allow for an attrition rate of approximately 25% (i.e., cancer survivors who discontinue participation in the study entirely, including failure to complete the follow-up questionnaires) and to enable subgroup analyses.

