### Randomization

After signing the informed consent form for study participation and completion of the baseline questionnaire, randomization will be performed by the study leader ([name]) or a research assistant using Castor EDC (https://www.castoredc.com), a Good Clinical Practice (GCP-)approved online tool, to divide cancer survivors in either the STEPS intervention or usual care control group. Variable block randomization will be applied with stratification per recruiting hospital. In Castor EDC, allocation sequence is concealed. However, due to the nature of the intervention, neither cancer survivors nor those who deliver the intervention or analyse the results will be blinded to the randomization. All cancer survivors randomized to one of the two trial arms will be considered to be included in the study, and will thus be followed during the follow-up period.

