#### RCT among cancer survivors

The primary outcome (i.e., working hours per week) will be assessed by asking cancer survivors about their current number of actual working hours. Hence, the primary outcome ranges from zero hours (for those on full sick leave) up to the number of working hours per week in the participant’s employment contract (for those fully returned to their work). This outcome was chosen as, according to the Dutch system, RTW is typically characterised by a gradual increase in work hours, while this measure is also important for workers trying to retain work. Secondary outcomes measures include: change in working hours (as a percentage of the contract hours at baseline), employment status (at work/not at work), sickness absence days, RRTW, work ability, health-related work functioning (only for cancer survivors who returned to work), time to RTW (only for cancer survivors who were on sick leave at baseline), and health-related quality of life. In addition to abovementioned outcome measures, information on a number of additional parameters (see Table 1 for a full overview) will be gathered, to describe the study sample, to include as potential confounder(s), and/or to conduct subgroup analyses.

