### Statistical analyses

For hardcopy questionnaires, data entry will be verified by a 10% double data entry check. In preliminary analyses, for both the RCT and cohort study, item frequencies and missing data will be examined. Patterns of missing data will be assessed to determine non-ignorable dropout. Scores for the included scales will be calculated according to established scoring algorithms (as described in more details in Table 2). All analyses will be performed using SPSS 22.0 [45], and a two-tailed significance level of 0.05 will be considered statistically significant.

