#### RCT among cancer survivors

Representativeness of participants will be evaluated by comparing cancer survivors who are included in the RCT with aggregated data of all potentially eligible cancer survivors from the NCR, using students’ t-test or appropriate non-parametric tests for the following characteristics: gender, age, time of diagnosis, tumour type and stadium and treatment. Moreover, reason of non-response at baseline (from the answer card) and during the follow-up period will be tabulated to get a better understanding of the representativeness of the study sample.

Baseline sociodemographic and clinical characteristics of the intervention group and the control group will be described and compared. Primarily, all analyses will be conducted on an intention-to-treat basis. In addition, per-protocol analyses will be carried out, in which only cancer survivors who fully complete the intervention according to protocol (i.e., having completed a minimum of three sessions: an introductory session, at least one one-on-one session with an occupational therapist, and at least one session with the reintegration consultant) will be compared to the control group.

To evaluate between-group differences on the aforementioned primary and secondary outcomes, generalized estimating equations (GEE) for longitudinal data (i.e., with the primary and secondary outcomes at six (T1) and 12 months of follow-up (T2)) will be used, adjusted for baseline values of the outcome and using appropriate tests for ordered and continuous data. This approach accounts for correlated within-subject responses, allows for non-normally distributed variables and deals adequately with missing data [46–48]. If the data are not missing completely at random, non-ignorable drop-out will be adjusted for [49]. Short- (T1) and long-term (T2) effects of the intervention will be reported separately. Effect sizes will be expressed in beta, with 95% confidence interval.

The secondary outcome ‘time to RTW’ will be analysed with time-to-event analysis [50]. A Kaplan-Meier curve will be drawn, and differences between the two groups will be tested with the log rank test. In addition, the Cox proportional hazard model of survival analysis will be applied to estimate hazard ratios and the corresponding 95% confidence intervals.

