For all analyses, unadjusted models and models adjusted for relevant confounders will be presented. In addition to the main analysis described above, subgroup analyses will be performed (see Table 1 for a list of potential confounders and subgroups). No interim analyses will be conducted for this study, as due to the low risk of the intervention it is unlikely that results of such analyses would lead to termination of the study.

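### The stated primary GEE adjusts only for baseline working hours; leaving out recruiting hospital and baseline contract hours gives up some precision

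*Protocol article*

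**What the plan says.** All references are to the protocol article.

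- **Randomization:** "Variable block randomization will be applied with stratification per recruiting hospital". Under Care as usual, the article adds that what the control group receives differs between hospitals.
- **Measurements, RCT among cancer survivors:** the outcome is bounded on both sides: "Hence, the primary outcome ranges from zero hours (for those on full sick leave) up to the number of working hours per week". That ceiling is set by each person's contract. Participants and recruitment admits anyone with at least 8 contracted hours per week and states no upper limit.
- **Table 2:** contractual hours at baseline are collected. Their only stated use is as the denominator of a secondary outcome, change in working hours in percent.
- **Statistical analyses, RCT among cancer survivors:** the GEE for the T1 and T2 outcomes is "adjusted for baseline values of the outcome and using appropriate tests for ordered and continuous data". The section then says that "unadjusted models and models adjusted for relevant confounders will be presented" and points to Table 1 for the candidates. Table 1 lists contract type (fixed or temporary), but neither contract hours nor hospital.
- **Sample size calculation:** "a between group (intervention versus control) effect of 5.5 h per week is expected", with an SD of 13 h and 80% power. This gives 88 per group (176 in total), with 236 to be recruited for about 25% attrition.

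**The concern.** **Hospital.** Stratified blocks balance the arms within each hospital, so differences in mean hours between hospitals do not contribute to the error of the treatment comparison. A model without hospital still counts those differences as residual noise. Its reported standard error is then larger than the true one, and the test is conservative.

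**Contract hours.** Everyone on full sick leave at entry has a baseline of 0 h. The one covariate in the model therefore cannot tell an 8 h contract from a 40 h contract, although the highest value each person can reach differs fivefold. Contract hours carry that information and are already in the baseline questionnaire. For participants at work, baseline hours convey part of it; for those on full leave they convey none.

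At stake is the width of the confidence interval for the primary effect. The article fixes an adjustment set and cites a candidate list, and both omit these two variables.

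**Working it through.** **1. Reproduce the planned sample size.** Inputs from Sample size calculation: difference 5.5 h, SD 13 h, power 80%. From Statistical analyses: "a two-tailed significance level of 0.05 will be considered statistically significant".

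n per arm = 2 × (1.960 + 0.842)² × 13² / 5.5² = 2 × 7.849 × 169 / 30.25 = 87.7, so 88 per arm and 176 in total, as stated. Attrition: 176 / 0.75 = 234.7, so 235 against 236 stated.

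Power at 88 per arm: SE = 13 × √(2/88) = 1.960; 5.5 / 1.960 = 2.806; Φ(2.806 − 1.960) = 80.1%.

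The SD of 13 h enters with no reduction for covariates. The article does not say whether it is marginal or residual after baseline adjustment.

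**2. Effect of adding both covariates.** Let R² be the share of residual variance that hospital and contract hours explain beyond the stated model. The residual SD becomes 13 × √(1 − R²). The documents give no value for R², so the range is assumed.

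| Assumed R² | Residual SD (h) | SE ratio | n per arm for 80% | Power at 88 per arm |
|---|---|---|---|---|
| 0 | 13.00 | 1.000 | 88 | 80.1% |
| 1% | 12.93 | 0.995 | 87 | 80.5% |
| 2% | 12.87 | 0.990 | 86 | 80.9% |
| 5% | 12.67 | 0.975 | 84 | 82.1% |
| 10% | 12.33 | 0.949 | 79 | 84.1% |
| 15% | 11.99 | 0.922 | 75 | 86.1% |
| 20% | 11.63 | 0.894 | 71 | 88.1% |

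Example for 20%: √0.80 = 0.894; SE = 1.960 × 0.894 = 1.753; 5.5 / 1.753 = 3.138; Φ(3.138 − 1.960) = 88.1%.

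**3. Hospital alone.** Suppose hospitals explain a share ICC of the variance and blocking balances the arms within them. The true variance of the estimate is then (1 − ICC) times what a model without hospital reports. Actual alpha = 2 × [1 − Φ(1.960 / √(1 − ICC))]. Power without hospital = Φ(0.846 / √(1 − ICC)). The ICC values are assumed.

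| Assumed ICC | Actual alpha without hospital | Power without hospital | Power with hospital |
|---|---|---|---|
| 0.01 | 0.049 | 80.3% | 80.5% |
| 0.05 | 0.044 | 80.7% | 82.1% |
| 0.10 | 0.039 | 81.4% | 84.1% |

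Leaving hospital out never pushes alpha above 0.05, and the gain from including it is small unless the ICC is large.

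**4. Is the upper part of the range plausible for contract hours?** An illustrative simulation drew contract hours around a mean of 30 with an SD of 4 to 10 h, cut off at 8 and 40. It placed 30, 50 or 70% of participants on full sick leave at baseline and let the fraction of the contract worked at follow-up be independent of contract size. Contract hours then had a partial R² beyond baseline hours of 3.7% (SD 4, 30% on leave) to 20.9% (SD 10, 70% on leave). All these inputs are assumptions, and the simulated outcome SD (about 10 to 11 h) is below the planned 13 h. The result shows only that values of several percent are credible.

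**The case against.** **The article is a condensed protocol.** Covariate lists are commonly left to an analysis plan, and the wording on relevant confounders does not forbid hospital or contract hours. This stands as far as it goes. The point therefore rests on what the article does fix: an adjustment by the baseline outcome alone, and a cited candidate list without the trial's own stratification factor.

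**Contract size was considered.** Methodological considerations notes that a gain in hours means something different under full-time and part-time contracts, and answers with the percentage outcome. That outcome is secondary and does nothing for the precision of the primary one.

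**Stronger readings that the documents do not support:**

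- *The trial is underpowered or biased.* A reader might infer this from the word "omitted", but the sample size takes no credit for covariates and reproduces. Randomisation protects against bias with or without them.
- *The gain equals 10 to 33% more participants.* That follows from a partial correlation of 0.3 to 0.5 (1/0.91 = 1.10; 1/0.75 = 1.33). No such correlation is given.
- *Presenting two models lets the result be chosen.* The article commits to presenting both for all analyses and refers to the GEE as the main analysis. An explicit ranking is still worth adding.
- *Self-referred participants cannot be stratified.* The article says "cancer survivors will be recruited through social media channels", which might suggest that they have no recruiting hospital. Design and setting, however, confines the RCT to people treated in a participating hospital, so each has a hospital to stratify by. Only the word recruiting needs clarifying.
- *Usual care varies, so hospital must matter.* Variation in care does not show that mean working hours differ between hospitals.

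**Conclusion.** The point holds as one of efficiency. The stated primary model omits the stratification factor and a collected baseline variable that bounds the outcome. The consequences are unused precision and slightly conservative standard errors.

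Its size cannot be derived from the documents. Over an assumed 1 to 20% of residual variance explained, the gain runs from negligible (SE down 0.5%) to useful (SE down about 11%). Contract hours probably account for most of it. A change is worth making because it is nearly free, not because the planned analysis is invalid.

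**What to change.** - State the primary GEE as arm, time, arm by time, baseline working hours, baseline contract hours and hospital, with very small hospitals pooled by a rule fixed in advance.
- Label the unadjusted model, and any model with further confounders from Table 1, as secondary or sensitivity analyses.
- Clarify that self-referred participants are stratified by the participating hospital that treats them. A separate self-referred stratum is not needed.

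The cost is a change of analysis wording and no new data. The model gains a few parameters. How many depends on the number of hospitals, which is given in a supplementary file not shown; with about 176 participants expected to complete, this is the reason for the pooling rule.

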### STEPS intervention

STEPS is a multidisciplinary intervention based on the Stages of Change, and combines work-related occupational therapy and reintegration consultation, to support cancer survivors in their RTW and work retention. The STEPS intervention program was designed both bottom-up (i.e., theory-driven, using the Stages of Change model [11]) and top-down (i.e., by interviews with experts and cancer survivors, as described in more detail elsewhere ([name], [name], [name], [name], [name], [name]. Tailoring work participation support for cancer survivors using the Readiness for Return to Work scale: perspectives and opinions of (health care) professionals and cancer survivors. In preparation.)). The intervention will be delivered by both occupational therapists and reintegration consultants, who tailor the intervention content according to the Stages of Change as measured by the RRTW. Occupational therapists are working at the outpatient clinics of participating hospitals. Most occupational therapists involved in the delivery of STEPS have experience with work-related guidance of cancer survivors. Those who do not, have experience with providing other aspects of occupational therapy to cancer survivors. All involved occupational therapists received a half day STEPS intervention training and will participate in peer intervision sessions throughout the intervention period. Involved reintegration consultants in STEPS are employed at a private reintegration consultancy, specialized and experienced in work-related support of cancer survivors. Reintegration consultants were trained in the STEPS intervention content as well. The content of the STEPS intervention has been described in the 89-page STEPS intervention handbook (in Dutch, available in PDF upon request). The intervention was designed to be delivered face-to-face, but will also be available remotely (i.e., using video conferencing or telephone meetings) if necessary (e.g., in case of COVID-19 regulations).

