See Fig. 2 for a logic model of the STEPS intervention elements, and Supplementary file 2 for an overview of the intervention components per behavioural change stage. The STEPS intervention has a maximum duration of 6 months, during which cancer survivors receive a minimum of three and a maximum of nine sessions, depending on their work-related support needs. STEPS is aimed at supporting cancer survivors’ work-related self-efficacy during their RTW or work retention process, and to encourage them to develop and maintain effective communication with their employer. During the STEPS intervention, the cancer survivors’ behavioural change stage will be monitored continuously and the intervention will be tailored to the specific stage the survivor is in. To do so, cancer survivors will be asked to complete a brief questionnaire (i.e., a Dutch version [25] of the Readiness for Return To Work - RRTW [15]) and an abbreviated version of the Return to Work Obstacles and Self-Efficacy Scale - ROSES [26]) prior to each session with the occupational therapist. Based on the outcomes of the RRTW questionnaire, participants will be categorised according to one of the six stages of change (pre-contemplation, contemplation, preparation: self-evaluative, preparation: behavioural, uncertain and proactive maintenance). Within each of these stages, participants will furthermore be given a traffic light designation (i.e. red, orange or green), based on the outcomes of the ROSES questionnaire, depicting potential barriers and facilitators regarding sustained employment and their overall progress within the intervention. Based on this categorisation the occupational therapist can, using the STEPS handbook, tailor the intervention provided (see Supplementary File 2).

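### STEPS participants share therapists and consultants, but the sample size assumes independence and the GEE is described as handling within-person correlation only; with any provider ICC above zero, precision and power are overstated

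*Protocol article*

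**What the plan says.** All references are to the protocol article.

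- **Randomisation.** Individual survivors are allocated in variable blocks, stratified by recruiting hospital.
- **STEPS intervention.** Two kinds of provider deliver the programme. On the first, the article says "Occupational therapists are working at the outpatient clinics of participating hospitals". A survivor has one introductory session and one to six further sessions with this therapist, so two to seven in all. The therapist adapts the content to the survivor's stage: "Based on this categorisation the occupational therapist can, using the STEPS handbook, tailor the intervention provided". There are also one or two sessions with a reintegration consultant from a private consultancy.
- **Care as usual.** Work-related care in hospitals is described as unstructured and limited, and it varies by hospital. It sometimes comes from occupational therapists, among others.
- **Sample size calculation (RCT).** The inputs are "a standard deviation of 13 h per week was assumed" and "a between group (intervention versus control) effect of 5.5 h per week is expected", "with a power of 80% and level of statistical significance set at" 0.05. The result is "the sample size required is 88 cancer survivors in each group (176 in total". Recruitment is raised to 236 for about 25% attrition and to allow subgroup analyses. No ICC, caseload or design effect appears.
- **Statistical analyses (RCT).** Outcomes at 6 and 12 months are analysed by GEE, adjusted for the baseline value. The stated reason is "This approach accounts for correlated within-subject responses, allows for non-normally distributed variables and deals adequately with missing data". No term for therapist, consultant or hospital is named.

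**The concern.** Survivors treated by the same therapist share whatever that therapist does better or worse than colleagues. Their outcomes can therefore be correlated in a way that has no full counterpart in the control arm. This is a partially nested design. The article itself allows for variation in delivery: content is tailored, therapists differ in prior experience of work-related guidance, and the process evaluation will assess whether delivery followed protocol.

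A standard error built from independent participants leaves out the between-therapist part of the variance in the STEPS arm. The trial aims to offer STEPS as an addition to standard care, so the natural target is the effect with therapists in general. For that target, the intervals at 6 and 12 months would be too short, and an apparent benefit would be declared more often than the nominal 5% when the average effect is zero. Stratifying by hospital does not remove the problem, and neither would a hospital main effect: it is common to both arms, while the therapist effect arises mainly in one.

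**Working it through.** **Inputs from the article:** SD 13 h; difference 5.5 h; power 80%; "a two-tailed significance level of 0.05 will be considered statistically significant"; 88 evaluable per arm; 236 recruited; attrition about 25%.

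**Assumptions, because the article gives no figure:** k = 6, 10 or 20 therapists with equal caseloads m = 88/k; therapist ICC of 0.01, 0.05 or 0.10; clustering in the STEPS arm only.

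**Step 1: reproduce the plan.**
n per arm = 2 × 13² × (1.960 + 0.842)² / 5.5² = 87.7, rounded up to 88. This matches exactly, and power at 88 is 80.1%. The formula has no clustering term, so the plan assumes full independence.
Reserve: 236 × 0.75 = 177 evaluable against 176 required. Attrition uses up the extra recruitment.

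**Step 2: add therapist clustering.**
- Design effect in the STEPS arm: DE = 1 + (m − 1) × ICC
- True standard error: SE = 13 × √[(1 + DE)/88]
- Standard error under independence: SE₀ = 13 × √(2/88) = 1.960 h
- Ratio R = SE/SE₀ = √[(1 + DE)/2]
- Actual two-sided error of the independent-participant test: 2 × [1 − Φ(1.960/R)]
- Power of a test using the correct SE: Φ(5.5/SE − 1.960)

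Worked case, k = 10 and ICC 0.05: m = 8.8; DE = 1 + 7.8 × 0.05 = 1.39; R = √(2.39/2) = 1.093; SE = 2.142 h; error = 2 × [1 − Φ(1.793)] = 7.3%; power = Φ(2.567 − 1.960) = 72.8%.

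| Therapists | ICC | DE | R | Error rate | Power, unadjusted |
|---|---|---|---|---|---|
| 20 | 0.01 | 1.03 | 1.01 | 5.2% | 79% |
| 20 | 0.05 | 1.17 | 1.04 | 6.0% | 77% |
| 20 | 0.10 | 1.34 | 1.08 | 7.0% | 74% |
| 10 | 0.01 | 1.08 | 1.02 | 5.4% | 79% |
| 10 | 0.05 | 1.39 | 1.09 | 7.3% | 73% |
| 10 | 0.10 | 1.78 | 1.18 | 9.6% | 66% |
| 6 | 0.01 | 1.14 | 1.03 | 5.8% | 77% |
| 6 | 0.05 | 1.68 | 1.16 | 9.1% | 68% |
| 6 | 0.10 | 2.37 | 1.30 | 13.1% | 58% |

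Simulation at ICC 0.05 (20,000 runs per setting) gave error rates of 9.5%, 7.3% and 5.7% for 6, 10 and 20 therapists. A partially nested test with small-sample degrees of freedom held 4.9–5.2%, with power of 60%, 69% and 75%. That is lower than the formula because few therapists means few degrees of freedom.

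**Step 3: credit the planned baseline adjustment.**
If baseline and follow-up hours correlate at r, both SE and SE₀ shrink by √(1 − r²). At k = 10 and ICC 0.05, power becomes Φ[5.5/(2.142 × √(1 − r²)) − 1.960]: 76.8% at r = 0.3 and 84.2% at r = 0.5. The stated power is regained when 1 − r² = 2/2.39, that is r = 0.40. The ratio R does not change if the residual ICC stays the same, so the 7.3% stays.

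**Step 4: allow for a hospital effect common to both arms.**
With one therapist per hospital, 9 therapists and ICC 0.05, simulated error was about 8.1%. It was about 7.3% when a shared hospital effect (ICC 0.05) was added and left unadjusted. The inflation shrinks but remains.

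**The case against.** **The quoted sentence is true, and the article is condensed.** GEE does handle within-person correlation, nothing excludes a further term, and an analysis plan not shown could add one. This stands in part: the analysis half of the point concerns the method as described. The sample-size half is settled by the reproduced 88.

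**The consequences are conditional.** A reader might infer that the interval is too narrow and the trial underpowered as plain facts. The documents do not support that, since they state neither an ICC nor a therapist count. The 89-page handbook, the training and the peer intervision sessions all point towards limited variation between therapists. At ICC 0.01 the effect is negligible. This stands.

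**Controls may see therapists too.** It is tempting to say that only STEPS participants share providers. The section on usual care says otherwise, although it describes such care as limited. The clustering is strongly unequal between arms, not absent in one.

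**The false-positive claim depends on the target.** If STEPS does nothing with any therapist, there is no STEPS-only therapist variance and the usual test holds its level. Inflation needs an average effect of zero with real differences between therapists, and a conclusion meant for therapists beyond those in the trial. That target fits the stated aim of adding STEPS to standard care, but it has to be stated.

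**Baseline adjustment may restore power.** It may, as step 3 shows, and the sample size does not credit it. It therefore cannot be said that final power falls below 80%. The standard error is not repaired.

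**A simple therapist model is incomplete.** Consultants are a second shared provider, intention-to-treat non-attenders have no treating therapist, and a linear mixed model does not suit dichotomous or ordinal outcomes. The fix has to deal with all three.

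**Conclusion.** The point holds in conditional form. STEPS participants share providers, the sample size makes no allowance for it, and the GEE is described as handling within-person correlation only. If the provider ICC is above zero and the conclusion is to extend beyond the participating therapists, the interval for working hours is too narrow and 80% power does not hold on the unadjusted basis on which it was calculated.

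With an assumed 10 therapists and 88 per arm, the size runs from negligible at ICC 0.01 to material at ICC 0.05: standard error understated by about 9%, error about 7.3%, power about 73%. Fewer therapists or a higher ICC make it worse, and more therapists make it milder. These figures assume equal caseloads and that every STEPS participant attends. They leave out clustering by consultant, whose caseloads are not stated. The change is worth making because it is cheap and because provider identity may be hard to recover if it is not recorded during delivery.

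**What to change.** 1. **Data.** Record the treating occupational therapist and reintegration consultant for each STEPS participant.
2. **Working hours.** Fit a partially nested model. Fixed effects: baseline hours, recruiting hospital, time, arm and arm-by-time. Random effects: patient, and therapist in the STEPS arm only. Use small-sample degrees of freedom.
3. **Participants without a therapist.** Controls form singleton clusters. For STEPS participants who never attend, decide in advance either to treat them as singletons or to assign them to the therapist planned at their hospital.
4. **Consultants.** Check clustering by consultant in a sensitivity analysis.
5. **Dichotomous and ordinal secondary outcomes.** Keep the GEE, with the therapist as the cluster in the STEPS arm and a robust variance.
6. **Sample size section.** State that 80% power assumes no provider clustering, and give the power over an assumed ICC range (for example 0.01–0.05) with the actual number of therapists. Leave enrolment as it is.

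The cost is two provider identifiers per STEPS participant, a changed model statement and a restated power figure. The interval will be somewhat wider and the stated power less favourable. With few therapists, the therapist variance will itself be estimated imprecisely, which is why the small-sample correction is needed.

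### The missing-data rule treats any departure from MCAR as non-ignorable drop-out, relies on a check that cannot tell MAR from MNAR, and so can leave the primary estimate biased

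*Protocol article*

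**What the plan says.** Three statements in the Statistical analyses section of the Protocol article form the missing-data plan for the trial.

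- In the general paragraph: "Patterns of missing data will be assessed to determine non-ignorable dropout".
- In the subsection on the RCT, of a GEE model for the 6-month (T1) and 12-month (T2) outcomes adjusted for the baseline value of the outcome: it "deals adequately with missing data".
- Directly after that: "If the data are not missing completely at random, non-ignorable drop-out will be adjusted for". The method of adjustment is given by citation only.

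The same section promises both unadjusted and confounder-adjusted models for all analyses. The Sample size calculation recruits 236 participants "to allow for an attrition rate of approximately 25" per cent, and describes attrition as people who leave the study altogether. The Randomization section says that participants are not blinded.

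**The concern.** Each of the three statements is faulty in itself.

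1. **The rule.** Departures from MCAR include MAR, where missingness depends only on observed data. MAR is ignorable for likelihood and imputation methods. The article goes straight from MCAR to non-ignorable drop-out, so any evidence against MCAR would trigger an MNAR correction.
2. **The check.** Observed patterns can give evidence against MCAR. They cannot separate MAR from MNAR, because the difference lies in the unobserved hours. The check cannot do what the article asks of it.
3. **The claim for GEE.** Unweighted GEE generally needs MCAR, or missingness that depends only on covariates in the model.

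The primary between-group difference in weekly hours is at stake. About 59 of 236 participants (25%) are expected to be lost. Because participants know their allocation, the reasons for leaving could differ by arm. Bias could then go in either direction.

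**Working it through.** **Inputs from the article.** The primary outcome is weekly hours: "The RCT sample size calculation is based on the primary self-reported outcome measure, i.e., working hours per week". For the size of effect: "a standard deviation of 13 h per week was assumed, and a between group (intervention versus control) effect of 5.5 h per week is expected". Power is 80%, and "a two-tailed significance level of 0.05 will be considered statistically significant".

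**The plan's own figure.** n per arm = 2 × (1.960 + 0.842)² × 13² / 5.5² = 87.7, so 88 per arm and 176 in total, as stated. Allowing for attrition, 176 / 0.75 = 234.7, so 235 against the stated 236. The sample size is not in question.

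**Assumptions that are not in the article.** Outcomes are normal with SD 13 h, the true effect is 5.5 h, and 25% are missing. Drop-out follows a logistic model with log-odds slope 1 per SD of its driver. Real hours are bounded between zero and contract hours, so normality is a simplification.

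**Check A: both follow-ups missing, drop-out driven by a baseline variable left out of the model.** This matches the article's description of attrition. The omitted variable (fatigue, for example) correlates 0.4 with follow-up hours. Baseline hours are in the model and correlate 0.5 to 0.6 with follow-up hours.

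| Drop-out slope | Omitted variable's correlation with baseline hours | Estimate, variable omitted | Estimate, variable included |
|---|---|---|---|
| one arm only | 0 | 4.4 h | 5.5 h |
| one arm only | 0.2 | 4.6 h | 5.5 h |
| one arm only | 0.4 | 4.9 to 5.0 h | 5.5 h |
| one arm only, sign reversed | 0 to 0.4 | 6.1 to 6.6 h | 5.5 h |
| same in both arms | 0 to 0.4 | 5.5 h | 5.5 h |

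The downward bias runs from 5.5 − 5.0 = 0.5 h to 5.5 − 4.4 = 1.1 h.

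In terms of power, with 88 per arm the SE is 13 × √(2/88) = 1.960 h.

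- At 5.5 h: Φ(5.5/1.960 − 1.960) = 80%.
- At 5.0 h: Φ(5.0/1.960 − 1.960) = 72%.
- At 4.4 h: Φ(4.4/1.960 − 1.960) = 61%.

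With the sign reversed, the effect would be overstated instead.

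**Check B: T1 complete, 25% missing at T2.** Assumed correlations are 0.6 (T0–T1), 0.5 (T0–T2) and 0.7 (T1–T2), with 400,000 subjects per scenario and simulation error of about 0.05 h. The table gives the T2 estimate against a true 5.5 h.

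| T2 drop-out depends on | GEE, independence | GEE, exchangeable | Likelihood |
|---|---|---|---|
| nothing (MCAR) | 5.49 | 5.50 | 5.50 |
| baseline hours | 5.45 | 5.45 | 5.45 |
| baseline hours, opposite slopes by arm | 5.55 | 5.56 | 5.56 |
| T1 hours, same slope | 5.21 | 5.47 | 5.50 |
| T1 hours, intervention arm only | 6.63 | 5.67 | 5.58 |
| T1 hours, opposite slopes by arm | 7.84 | 5.79 | 5.53 |
| T2 hours (MNAR), same slope | 4.90 | 5.07 | 5.08 |
| T2 hours (MNAR), intervention arm only | 7.45 | 6.85 | 6.81 |
| T2 hours (MNAR), opposite slopes by arm | 9.76 | 8.48 | 8.42 |

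Drop-out driven by baseline hours causes no material bias, because baseline hours are in the model. Drop-out driven by T1 hours biases GEE by −0.3 to +2.3 h under independence, but by at most about 0.3 h under exchangeable correlation. Under MNAR the likelihood model is biased about as much as exchangeable GEE.

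**The case against.** A reader might infer that the primary estimate will be biased under the kind of drop-out to be expected here. The documents do not support that reading, for four reasons.

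- The article does not rest on GEE alone. It promises an adjustment when data are not MCAR. The details of that method and the choice of working correlation may properly be left to the full protocol or the analysis plan.
- It also plans confounder-adjusted models, and Table 1 lists fatigue at baseline among the additional variables. The baseline outcome is therefore not the only covariate that might be used.
- No section says which drop-out mechanism is expected, or that it differs by arm.
- The bias in Check A is not specific to GEE. People with no follow-up add no post-baseline data to either a GEE or a mixed model, so a likelihood model with the same covariates has the same bias.

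All four points stand, and they limit the size and certainty of the concern. They do not rescue the rule. A fuller document could name the adjustment, but it would still have to replace the step from not MCAR to non-ignorable, and the check said to establish it. The confounder-adjusted models help only if they include the predictors of drop-out, and the article does not select covariates on that ground.

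**Conclusion.** The missing-data rule is wrong as stated and should be replaced: it skips MAR, relies on a check that cannot identify non-ignorable drop-out, and overstates what unweighted GEE can do.

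The effect on the primary estimate is conditional. Bias can arise in two ways: drop-out differs by arm and depends on baseline variables outside the model, or T2 drop-out depends on T1 hours and an independence working correlation is used. Under the assumptions of Check A, the first route gives about 0.5 to 1.1 h of 5.5 h, in either direction, and nothing when the slopes are equal in both arms. The second route reaches 2.3 h only with opposite drop-out slopes by arm under independence. All these sizes rest on assumed slopes and correlations, not on figures from the article.

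**What to change.** 1. Delete the rule that data which are not MCAR call for a non-ignorable adjustment, and the statement that patterns of missing data determine non-ignorable drop-out. Patterns can still be described.
2. Make the primary analysis valid under MAR, using variables that Table 1 already collects at T0, such as fatigue, work ability, sick leave and treatment. Either impute multiply by arm before the GEE, or fit a likelihood mixed model that includes these predictors of drop-out. Replacing GEE by a mixed model without them does nothing for people who miss both follow-ups.
3. Prespecify one MNAR sensitivity analysis, such as a delta shift of imputed hours, and report where the conclusion changes.

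The cost is revised wording and slightly more analysis work. No new data are needed and the sample size does not change.
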